## Abstract

**Aim::**

The Pain Recognition and Evaluation to Validate Effective Neck and back Treatment (PREVENT) study aims to identify cognitive, behavioral, and treatmentrelated predictors of chronic musculoskeletal pain (CMP) development following emergency department (ED) care for acute neck or back pain after trauma.

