Despite the ED’s important role in addressing pain across the acute-chronic continuum, limited research has examined ED-specific risk factors contributing to the transition from acute to chronic pain, and few interventions have been systematically implemented to prevent this trajectory. In the general population, the annual incidence of chronic pain is 6.3% (Nahin *et al.*, 2023), but among ED patients with acute pain, the risk of chronic pain transition is substantially higher, ranging from 12%–27% (Beaudoin *et al.*, 2020; Office of the Assistant Secretary for Planning and Evaluation, 2021; Bourassa *et al.*, 2020; Barnett *et al.*, 2017), underscoring the ED as a critical setting for early identification and prevention. Prior ED-based studies have identified predictors such as pain intensity, body region, and opioid use (Beaudoin *et al.*, 2020; Office of the Assistant Secretary for Planning and Evaluation, 2021; Bourassa *et al.*, 2020; Barnett *et al.*, 2017), but the role of maladaptive pain beliefs, kinesiophobia, pain catastrophizing, and guideline-discordant care remains largely unexplored. Evidence from post-surgical and outpatient populations has established that these psychological factors and guideline-discordant care (e.g., excessive imaging) are associated with an increased risk of developing chronic pain (Theunissen *et al.*, 2012; Stevans et al., 2020), and this is further supported by observational and conceptual studies linking these factors to pain persistence, negative affect, and pain-related disability (Rogers & Farris, 2022; Coninx *et al.*, 2025; Ray *et al.*, 2022; Keller *et al.*, 2023; Brown *et al.*, 2020; Vivekanantha *et al.*, 2023). However, their potential value in ED-based screening and intervention remains untested.

The overarching goal of this study is to determine whether maladaptive pain beliefs, fear-avoidance behaviours, catastrophizing, and guideline-discordant care contribute to the transition from acute to chronic pain among ED patients with acute post-traumatic musculoskeletal pain. We hypothesize that individuals who transition to CMP will exhibit greater psychological distress (e.g., anxiety, depression, pain catastrophizing), misinformed pain beliefs (e.g., kinesiophobia), higher rates of non-prescribed psycho-active substance use (e.g., alcohol, marijuana), and distinct patterns of ED-based pain management (e.g., increased imaging and pharmacologic interventions).

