Quantitative statistical analysis will involve predictive model development using multivariable logistic regression to identify significant predictors of CMP as a binary outcome. Pain beliefs will be modelled as the primary independent variable, with adjustment for potential confounding variables identified in the conceptual framework (e.g., demographics, anxiety, depression, substance use, and social determinants of health). Mediation analyses will explore indirect pathways through cognitive-affective constructs (e.g., pain catastrophizing, fear-avoidance, recovery expectations, and pain self-efficacy) and behavioural responses (e.g., physical activity), using structural equation modelling or mediation analysis to estimate direct and indirect effects. Interaction terms between pain beliefs and demographic variables will be tested to evaluate potential effect modification. Model validation will incorporate cross-validation techniques, such as k-fold cross-validation, to assess robustness. Receiver operating characteristic (ROC) curve analysis will determine the model’s discriminative ability using area under the curve (AUC) estimates, and calibration analysis (e.g., Hosmer–Lemeshow test) will assess model fit. Preliminary clinical cut-offs for pain beliefs scores will also be explored by identifying thresholds that maximize sensitivity and specificity for predicting CMP developed based on ROC analysis. Sensitivity analyses will evaluate the stability of findings under alternative variable definitions and measurement criteria.

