## Conclusion

This research will advance our understanding of the biopsychosocial factors influencing the transition from acute to chronic neck and back pain, particularly within the ED setting. By identifying modifiable psychological and behavioural risk factors – such as maladaptive pain beliefs, fear-avoidance, and low self-efficacy – this study will lay the groundwork for the development of targeted, evidence-informed interventions. Specifically, findings may inform the adaptation of existing frameworks, such as SBIRT for pain management and enable the tailored delivery of PSE to high-risk patients. These approaches could reduce recurrent ED visits, improve long-term patient outcomes, and support the integration of preventative strategies into clinical guidelines and health policy. As a foundational study, this work will also support larger-scale trials and public health efforts to reduce the burden of CMP.

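### One logistic regression is both the adjusted model for pain beliefs and the prediction model, so the prediction model lacks predictors the study sets out to identify

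*Protocol article*

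**What the plan says.** All references are to the protocol article.

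- **Sample size & quantitative data analysis, first role.** The regression is "predictive model development using multivariable logistic regression to identify significant predictors of CMP as a binary outcome".
- **Same section, next sentence, second role.** "Pain beliefs will be modelled as the primary independent variable, with adjustment for potential confounding variables identified in the conceptual framework". The examples of confounders are "demographics, anxiety, depression, substance use, and social determinants of health".
- **Same section, mediators.** "Mediation analyses will explore indirect pathways through cognitive-affective constructs", and through physical activity, by structural equation modelling or mediation analysis.
- **Same section, scoring.** Cross-validation, AUC and calibration are applied to the model. No second regression with its own candidate list is described.
- **Abstract, Aim.** The study "aims to identify cognitive, behavioral, and treatmentrelated predictors of chronic musculoskeletal pain (CMP) development".
- **Introduction.** The goal is to "determine whether maladaptive pain beliefs, fear-avoidance behaviours, catastrophizing, and guideline-discordant care contribute to the transition from acute to chronic pain".
- **Quantitative outcomes & assessment tools.** Table 1 labels beliefs as the independent variable, five measures as mediators, and the rest as covariates or outcomes. A chart audit collects imaging, medication, disposition and referrals, but Table 1 gives these no analysis role.
- **Discussion and Conclusion.** Patients whom the predictive model flags as high risk are to be prioritised for a later intervention. The Conclusion claims groundwork for it "By identifying modifiable psychological and behavioural risk factors", and names fear-avoidance and low self-efficacy among them.

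**The concern.** The two roles call for different variables. To estimate the total association of beliefs with chronic musculoskeletal pain (CMP), the model should contain the confounders whatever their p-values and leave the mediators out. To predict CMP, it should be able to use any baseline variable that carries information, including the mediators and the care given in the ED.

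The text gives both roles to one regression and lists variables suited only to the first. The reported AUC and calibration would then describe beliefs plus confounders. A reader would take them as the performance of the screening model promised in the Discussion, although most of the factors in the stated aim were never candidates. If an analyst later repairs this by adding the missing variables to the same regression, the belief coefficient changes meaning without any change in its label.

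**Working it through.** **1. Variable sets side by side**

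| Variables | Role given in the document | In the regression as described? | Needed for the stated prediction aim? |
|---|---|---|---|
| Pain beliefs | Independent variable | Yes | Yes |
| Demographics, anxiety, depression, substance use, social determinants | Covariates | Yes | Yes, as candidates |
| Catastrophizing, fear-avoidance, self-efficacy, expectations, physical activity | Mediators | No, mediation analysis only | Yes (Abstract, Conclusion) |
| ED imaging, medication, referrals | None assigned | No, in no described model | Yes (Abstract, Introduction) |

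The last two rows are the gap.

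**2. Information available**

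The plan's own figures reproduce. With α = 0.05 two-sided (sidedness is assumed), power 0.80 and d = 0.2, ((1.960 + 0.842)/0.2)² = 196.2, rounded up to 197. Then 197 × 1.25 = 246.25, stated as 246. The 197 comes from a one-sample formula and was not derived for either model.

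- Completers at 25% attrition: 246 × 0.75 = 184.5.
- Events at 12%: 184.5 × 0.12 = 22.1.
- Events at 27%: 184.5 × 0.27 = 49.8.

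The parameter counts below are assumptions, since the document does not give the coding. Age, sex, comorbidity, anxiety and depression take 1 each, insurance 1 to 3, race/ethnicity 1 to 4, substance use 1 to 3, and social needs 1 to 5. That makes 9 to 20.

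- Beliefs plus confounders, 10 to 21 parameters: from 22.1/21 = 1.1 to 49.8/10 = 5.0 events per parameter.
- With five mediators, 15 to 26 parameters: from 22.1/26 = 0.9 to 49.8/15 = 3.3. ED-care variables would lower this further.

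A model that holds everything is thinly supported, so the prediction model needs a short list and shrinkage.

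**3. What adding the missing variables to the same model does (illustration only)**

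None of these coefficients comes from the document.

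- *Assumption set 1*: 400,000 simulated records, CMP rate 18%, one confounder, one mediator and one independent predictor. Beliefs plus confounder gives a belief OR of 1.52 per SD and an AUC of 0.68. Adding the mediator and the independent predictor raises the AUC to 0.74 and lowers the belief OR to 1.22.
- *Assumption set 2*: three mediators, each correlated 0.5 with beliefs, log OR 0.2 each, direct log OR 0.15. The total log OR is about 0.15 + 3 × 0.5 × 0.2 = 0.45, an OR of about 1.57. With the mediators in the model it is exp(0.15) = 1.16.

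Both falls restate the assumed direct effect. They show the direction when mediators carry part of the effect. They do not estimate an error in this plan.

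**The case against.** The strongest reply is that the document already keeps mediators apart. The adjustment list contains none, Table 1 labels them separately, the caption of Figure 1 distinguishes them from confounders, and they have their own analysis. That analysis also estimates paths from mediators to outcome, so fear-avoidance and self-efficacy could be named as risk factors there. An article may also leave detailed model specification to a fuller document.

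Most of this stands, and it rules out three stronger readings that a reader might infer:

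- *That the belief estimate will be over-adjusted and the primary question answered wrongly.* This needs mediators in the regression, and the text points the other way.
- *That variables will be selected by p-value, inflating the retained coefficients.* No selection rule is stated. Identifying significant predictors may mean only reporting which coefficients reach significance.
- *That no single set of variables can ever serve both purposes.* A confounder-adjusted model can be scored for AUC, and beliefs, the main hypothesised predictor, are in it. The difficulty arises here because this study counts mediators and treatment factors among the predictors it seeks.

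The reply does not remove the remaining point. A mediation analysis yields direct and indirect effects, not a validated risk model, and it gives the ED-care variables no place. Nor is the complaint about omitted detail: consecutive sentences give one regression two purposes, and a fuller plan that follows them inherits the mismatch.

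**Conclusion.** The point holds in limited form. Followed as written, the association of pain beliefs with CMP is broadly sound. The model scored by AUC and calibration, however, leaves out the five mediator measures and all ED-care variables, although the study's aim, its Conclusion and the planned risk targeting depend on factors of these kinds. Putting them into the same regression would change the belief coefficient from a total to a direct effect.

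This rests on reading the confounder examples as typical of the full adjustment set and on the absence of any other described prediction model. The shortage of information rests on the plan's own figures: about 22 to 50 events among about 184 completers, if attrition is 25% and the CMP rate lies between 12% and 27%. The size of any shift in the belief OR cannot be known from the document.

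**What to change.** State two models in place of one.

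- **Model A (primary association).** Month-0 pain beliefs plus a fixed set of month-0 confounders taken from the causal diagram, with no mediators and no selection on significance. The mediation analysis stays as a separate step.
- **Model B (prediction).** A short, pre-listed set of baseline candidates that includes the psychological and behavioural measures and the ED-care variables. Fit it with penalisation because only about 22 to 50 events are expected, and judge it by cross-validated AUC and calibration. Do not read its coefficients as effects.

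Reword the opening sentence of the analysis paragraph so that finding significant predictors is no longer the purpose of a single model, and say that the later risk targeting refers to Model B.

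The cost is revised wording and one more model fit on data already planned. The downside is that Model B's coefficients can no longer be reported as separate risk-factor effects.

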### Sample size & quantitative data analysis

Our primary outcome – pain frequency – is assessed as a categorical variable based on participants’ reported number of days per week experiencing neck or low back pain (0–1 days, 2–3 days, 4–5 days, or 6–7 days). Pain frequency will be assessed at 1, 3, and 6 months. For analysis, responses will be dichotomized to classify CMP status: participants reporting pain on 4–5 or 6–7 days per week will be categorized as having CMP (coded as 1), while those reporting 0–1 or 2–3 days per week will be categorized as not having CMP (coded as 0). Based on prior studies reporting a 12%–27% transition rate from acute to chronic pain (Beaudoin *et al.*, 2020; Office of the Assistant Secretary for Planning and Evaluation, 2021; Bourassa *et al.*, 2020; Barnett *et al.*, 2017), we conducted a power analysis to estimate the incidence of CMP with acceptable precision. Using a small effect size (Cohen’s d 0.2), with α = 0.05 and power = 0.80, a minimum sample size of 197 participants is required. To account for an estimated 25% attrition rate, we will recruit 246 participants to ensure adequate study power. This sample size will also provide sufficient power to explore the association between baseline pain beliefs and subsequent development of CMP, as well as to conduct preliminary analyses for establishing potential clinical cut-offs on pain relief measures. Higher scores may indicate individuals at elevated risk for developing CMP and who may benefit from targeted educational interventions. However, these exploratory analyses will require validation in independent samples.

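### Belief-score cut-offs are chosen on 22 to 50 expected events with no correction stated for the search: sensitivity would be overstated by about 5 to 11 points, and the claim of sufficient power for cut-offs has no calculation behind it

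*Protocol article*

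**What the plan says.** Everything relevant is in the protocol article under Sample size & quantitative data analysis.

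- **Selection rule.** Cut-offs on the belief score are to be found by "identifying thresholds that maximize sensitivity and specificity for predicting CMP". The thresholds come from the ROC analysis of the study data.
- **Internal validation.** "Model validation will incorporate cross-validation techniques, such as k-fold cross-validation, to assess robustness". The sentence concerns the multivariable model. The later cut-off sentence concerns the belief score and names no resampling step.
- **Adequacy claim.** "This sample size will also provide sufficient power to explore the association between baseline pain beliefs and subsequent development of CMP". The same sentence then extends the claim to preliminary work on possible clinical cut-offs. There it names pain relief measures, although the analysis paragraph speaks of belief scores.
- **Caveat.** The same paragraph ends by calling these analyses exploratory and asking for confirmation in separate samples.
- **Event rate.** "Based on prior studies reporting a 12%–27% transition rate from acute to chronic pain".
- **Size.** The inputs of the power calculation are given as "Using a small effect size (Cohen’s d 0.2), with α = 0.05 and power = 0.80", and the result is 197 before any allowance for loss to follow-up. The recruitment target then reads: "To account for an estimated 25% attrition rate, we will recruit 246 participants".

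**The concern.** A threshold picked because it gives the best sensitivity and specificity in one data set looks better in those data than it would in new patients. The bias grows as the number of events falls. The remedy is to include the search in the resampling, but the article ties cross-validation only to the model. The sample-size paragraph meanwhile tells the reader that the study is large enough for the cut-off work, while its only calculation is presented as one for the incidence of CMP.

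At stake is the sensitivity this study publishes for a belief-score cut-off. If it is too high, the share of later CMP cases that the cut-off would miss is understated. The article suggests that high scorers might be offered targeted education, so readers could take the published figure at face value.

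**Working it through.** **1. The plan's own figure.** The one-sample normal approximation, two-sided (sidedness is not stated), gives ((1.960 + 0.842)/0.2)² = 196.2, rounded up to 197. The recruited number matches 197 × 1.25 = 246.25, or 246. Both reproduce. The calculation contains no threshold, sensitivity or specificity, so it says nothing about cut-offs.

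**2. Expected events.**
- Completers: 246 × 0.75 = 184.5.
- Events: 184.5 × 0.12 = 22.1, and 184.5 × 0.27 = 49.8.
- With 197 completers: 23.6 to 53.2. With no attrition: 246 × 0.12 = 29.5 to 246 × 0.27 = 66.4. The picture changes little.

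**3. Precision even at a cut-off fixed in advance.** The 95% half-width for sensitivity is 1.96 × √(Se(1 − Se)/events).
- 22 events, Se 0.612: 1.96 × √(0.612 × 0.388/22) = 0.204, about ±20 points.
- 50 events, Se 0.626: 1.96 × √(0.626 × 0.374/50) = 0.134, about ±13 points.

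**4. Effect of choosing the cut-off in the same data.** The documents give no discrimination figure for the belief score, so the AUC is an assumption, varied from 0.61 to 0.80. An AUC of 0.61 corresponds to an odds ratio of about 1.5 per SD: Φ(ln 1.5/√2) = Φ(0.287) = 0.61. The simulation uses 184 patients, normal scores with equal SD in cases and non-cases, a mean difference of √2 × Φ⁻¹(AUC), and 4,000 replicates per setting. The cut-off maximises sensitivity + specificity − 1 (Youden index), the usual reading of the stated rule. Apparent values come from the selection data; true values are those of the same cut-off in the population.

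| Events | AUC | Sensitivity, apparent / true (%) | Specificity, apparent / true (%) | Youden overstated by | 95% range of cut-off (SD) |
|---|---|---|---|---|---|
| 22 | 0.61 | 65.9 / 55.0 | 60.1 / 58.6 | 0.12 | −0.9 to 1.4 |
| 22 | 0.70 | 71.4 / 61.2 | 66.4 / 65.4 | 0.11 | −0.4 to 1.3 |
| 22 | 0.80 | 78.1 / 69.3 | 73.9 / 73.1 | 0.10 | 0.0 to 1.4 |
| 50 | 0.61 | 63.1 / 56.8 | 59.7 / 57.3 | 0.09 | −0.7 to 1.2 |
| 50 | 0.70 | 68.3 / 62.6 | 66.4 / 64.6 | 0.08 | −0.3 to 1.1 |
| 50 | 0.80 | 75.9 / 70.9 | 73.9 / 72.4 | 0.07 | 0.1 to 1.2 |

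SD is the within-group SD, and zero is the mean of the non-cases.

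- Sensitivity is overstated by 8.8 to 10.9 points at 22 events and by 5.0 to 6.3 points at 50.
- Specificity is overstated by 0.8 to 2.4 points.
- The range of the cut-off is widest at 22 events and AUC 0.61 (1.4 + 0.9 = 2.3 SD) and narrowest at 50 events and AUC 0.80 (about 1.1 SD).
- At AUC 0.70 the chosen cut-off falls, in 95% of replicates, between the 32nd and 88th score percentiles with 22 events, and between the 32nd and 81st with 50.

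**The case against.** The strongest defence is that the article already limits what these cut-offs can be used for. It calls the work preliminary and exploratory and requires confirmation elsewhere, which is the standard remedy for a data-chosen threshold. It is also a condensed article, and how the search sits within the resampling could be left to a fuller analysis plan. Both points stand and lower the severity. Neither corrects the sensitivity that this study would itself report, and neither supports the claim of sufficient power, which the article states outright.

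Four stronger readings are tempting, and the material does not support them.

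- **That uncorrected figures from the same patients are planned.** The article does not say so. It is silent on whether the cross-validation covers the threshold.
- **That sensitivity and specificity are both clearly inflated.** Non-cases are numerous, so specificity moves by only 1 to 2 points.
- **That the cut-off is almost undetermined.** This comes close only for weak discrimination, near an AUC of 0.6. At AUC 0.70 with 50 events, half of the chosen cut-offs lie between the 48th and 67th percentiles: imprecise, but informative.
- **That the cut-off will select patients for Pain-SBIRT.** The Discussion links that selection to the predictive model, for which cross-validation is planned, and not to the belief-score threshold.

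**Conclusion.** The point holds as a narrow one of low severity. Followed as written, the threshold search would give an optimistic sensitivity, materially so near 22 events and modestly at 50, together with an imprecise cut-off. The statement that the sample size suffices for the cut-off work is unsupported. The primary outcome and the main regression model are not affected.

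The size rests on the article's own attrition and event rates, and on assumptions that it does not give: an AUC of 0.61 to 0.80, normal scores with equal spread, the Youden reading of the rule, and one search over a pooled neck and back score. A score rounded to tenths of an SD gives slightly less optimism (Youden 0.06 to 0.11 at AUC 0.60 to 0.70). Separate searches for the two questionnaires would leave fewer events in each.

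**What to change.** 1. State that the whole threshold search is repeated inside each bootstrap or cross-validation sample.
2. Make the optimism-corrected sensitivity and specificity the reported cut-off result, with a percentile interval for the threshold.
3. In the sample-size paragraph, withdraw the sufficiency claim for cut-offs and give the expected precision at 22 to 50 events instead. Keep the requirement for independent validation. In the same sentence, reconcile the reference to relief measures with the belief scores named in the analysis paragraph.

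The cost is a few lines of code and some changed wording, with no new data. The downside is slightly less favourable published figures.
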